### Setting and Sample

Our study settings are community-based continuing care systems. Each province provides access to a range of publicly funded community-based continuing care services, including adult day programs [55-63]. Each provincial health system determines and enacts access criteria and provides services (directly or via contracted providers) [55-63]. Day program eligibility is assessed in each province, using comparable processes, criteria, and assessments (ie, the Resident Assessment Instrument—Home Care [RAI-HC], a standardized, valid, reliable assessment tool [64]) [60,65,66]. To be eligible, attendees need to have not only some care dependency but also the ability to cope to some extent with activities of daily living, ambulate or transfer with no or minimal assistance, be continent or independent in managing continence products, exhibit no or easily manageable responsive behaviors, and either be alone for extended periods or have a caregiver who requires respite. Our study cohort will include all individuals aged 65 years or older with an initial RAI-HC assessment completed between January 1, 2012, and December 31, 2021. We will follow everyone until they move into a care home, are lost to follow-up (eg, because of death, moving out of province, loss of public insurance eligibility), or until December 31, 2024 (the end of the period covered by our data). That will allow for a care trajectory of at least 3 years (for those with an initial RAI-HC assessment in December 2021), enabling us to assess the number and characteristics of individuals with different day program use patterns, and compare them with those who were never exposed to a day program.

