### Sample Size Calculation

The yearly average number of completed RAI-HC assessments is ~20,000-30,000 in Alberta, ~34,000-39,000 in British Columbia, and ~10,000 in Manitoba [67]. About 50% of those assessed receive a reassessment within 12 months and another 10%-30% receive a reassessment after >15 months [68]. There are 89 publicly subsidized day programs in Alberta (~3300 spaces per day), 95 in British Columbia (~1500 spaces per day), and 70 in Manitoba (~1000 spaces per day) for a total of 254-day programs with 5800 spaces on any given day. Some day program users do not attend daily, but only 1 or a few days per week, so the number of unique attendees exceeds the number of spaces per day. This corresponds to >20,000 attendees per year (>200,000 within the study period), each with multiple assessments. Our study sample size will be large enough to detect small effects sizes. With Cox proportional hazards models, adjusted for covariates explaining an assumed 25% of effect variance (a=.05; power=0.8) [69], we require a total sample of 1327 participants to detect a hazard ratio for admissions to care homes of 0.6 (as can be expected based on a similar Canadian study [42]) in favor of day program attendees. Similarly, Kelly [43] was able to detect significantly fewer emergency department visits and hospital admissions per day among 812 day program attendees compared with 812 propensity score matched to nonattendees. Our expected sample size will be considerably larger than for those previous studies, allowing for complex statistical modeling.

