### Data Sources

For each individual in our cohort, designated provincial health system analysts will link all records available within the study time frame from the following databases: (1) regional continuing care registries, documenting when an individual starts or stops receiving any community-based continuing care, including day programs, how these services change over time, and when an individual is admitted to a care home. (2) Population registries for each participant’s demographic data. (3) RAI-HC assessments [64], completed annually for people receiving long-term home care (60+ days), and to determine day program eligibility. The RAI-HC will provide data on older adults’ medical conditions, functional dependence, pain, cognitive impairment, mood, and behavioral problems. It also includes information on a person’s marital or partnership status, caregiver availability, whether that caregiver lives with the older adult, and caregiver distress. Additional caregiver characteristics are not included in the available provincial databases, posing a limitation to our quantitative analyses. However, a related prospective cohort study that we are conducting in Ontario will allow us to link comprehensive caregiver and older adult data, and we are currently conducting additional qualitative research that will illuminate how caregiver characteristics may affect day program use and outcomes. (4) Discharge abstract database (DAD) for information on all inpatient hospital stays, including diagnoses and length of stay. (5) National Ambulatory Care Report System (NACRS) for all emergency department visits and diagnoses. In British Columbia, we will use the physician payment file in addition, since NACRS is not collected in all emergency departments [70]. (6) Pharmaceutical information on outpatient prescription medications filled through a community pharmacy and covered by provincial drug formulary. (7) Care provider claims data for health service claims submitted for payment by health care providers (eg, general practitioners, nurse practitioners, geriatricians, geriatric psychiatrists, neurologists, therapists) to obtain information on general and specialist health services used by participants.

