#### Objective 2: Compare Older Adults’ Characteristics by Day Program Use, Province, and Time

Using our full cohort of day program attendees and nonattendees, we will descriptively assess the distribution of sample characteristics over time and by province. In each province and quarter, we will report and plot graphically the proportion (95% CI) of individuals with each characteristic, stratified by day program use class versus nonuse. Using general estimating equations (GEEs) [83], we will assess whether the number of persons with each characteristic has changed over time and whether characteristics are associated with older adults’ day program use or nonuse pattern. We will run a separate GEE model for each characteristic within each province, with the respective characteristic as individual-level outcome. We will run binary logistic regressions for dichotomous variables (eg, sex) and ordinal regressions for categorical variables (eg, residential instability quintile). Models will account for repeated measures within individuals and include the independent variables year of assessment (to assess change in social determinants over time), use or nonuse class (to assess differences in social determinants by day program use), and an interaction between year and use or nonuse (to assess how social determinants differed between use and nonuse patterns by year). Using random-effects mixed regression models, we will pool provincial effects statistically. Other Pan-Canadian studies, such as the Canadian Network for Observational Drug Effect Studies [84], have successfully applied this approach and developed rigorous protocols to minimize bias and maximize consistency of regional analyses.

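### Objective 2 reads year of assessment as change over time, but the cohort takes entrants only in 2012-2021 and is followed to 2024, so calendar change is mixed with time in care and selective exit.

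*Protocol article*

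**What the plan says.** All places are in the protocol article.

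- **Setting and Sample** defines the cohort as people aged 65 or older "with an initial RAI-HC assessment completed between January 1, 2012, and December 31, 2021". They are followed to care home admission, loss to follow-up, "or until December 31, 2024 (the end of the period covered by our data").
- **Data Sources** describes the RAI-HC as "completed annually for people receiving long-term home care (60+ days"), so one person can contribute several records. **Sample Size Calculation** adds: "About 50% of those assessed receive a reassessment within 12 months", with another 10%-30% reassessed after more than 15 months.
- **Objective 2** under Statistical Analyses works on everyone: "Using our full cohort of day program attendees and nonattendees, we will descriptively assess the distribution of sample characteristics over time and by province". For the plots: "In each province and quarter, we will report and plot graphically the proportion (95% CI) of individuals with each characteristic", split by use class.
- The same section fits one GEE per characteristic and province. The listed independent variables are "year of assessment (to assess change in social determinants over time"), use or nonuse class, and their interaction. It lists no term for time since the first RAI-HC, entry year or age, and does not restrict the analysis to first assessments.

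**The concern.** Calendar year in this cohort is not neutral with respect to time in care. The cohort fills from 2012, closes to entry after 2021, and then only ages and shrinks. A characteristic that changes with time since entry will drift across calendar years even if nothing about the client population has changed. GEE deals with correlation between one person's records; it does not remove this confounding.

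Objective 2 covers characteristics of that kind: age, ADLh above 3, CPS above 3, caregiver items and partnership status. Sex is fixed, and area deprivation is assigned by postal code. Those two could drift only through selective exit or a move.

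At stake is the reading of the year term and the plots. Time is in the objective's title, and a paper on attendee characteristics over time is planned. Ageing of a closed cohort, or selective departure from it, could be published as a change in who uses community care. The year-by-class interaction is exposed too. Nonuse is defined over the whole care trajectory, and later entrants have less follow-up in which to become users. The size of that effect was not computed.

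**Working it through.** The article gives no figure for the Objective 2 trend, so there is none to reproduce. The check asks what the year term shows when the true calendar trend is zero.

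**From the article.** Entry 2012-2021, none in 2022-2024, follow-up to the end of 2024, and roughly annual assessments.

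**What follows from the dates alone.** Someone assessed in 2012 entered in 2012, so is under 1 year from entry. Someone assessed in January 2024 entered by December 2021 at the latest, so is at least 2 years from entry. No first assessments fall in 2022-2024.

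**Assumed (not in the article).** Equal entry each year; annual continuation probability s; prevalence 20% at entry, rising by g = 3 to 5 percentage points per year since entry; exit unrelated to the characteristic.

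**Formula.** In year t, the possible completed years since entry k run from max(0, t − 2021) to t − 2012, each with weight s^k. Mean time since entry is Σk·s^k / Σs^k, and prevalence is 0.20 + g × that mean. The odds ratio per year comes from a logistic fit of the weighted prevalences on year.

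With 30% exit (s = 0.7), mean k is 0 in 2012, 2.04 in 2021 and 5.04 in 2024. Prevalence is then:
- 2012: 20%
- 2021: 0.20 + 0.03 × 2.04 = 26%, to 0.20 + 0.05 × 2.04 = 30%
- 2024: 0.20 + 0.03 × 5.04 = 35%, to 0.20 + 0.05 × 5.04 = 45%

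| Exit per year | Mean k, 2021 | Mean k, 2024 | OR per year, 2012-2024 | OR per year, 2012-2021 only |
|---|---|---|---|---|
| 20% | 2.80 | 5.80 | 1.06-1.10 | 1.05-1.07 |
| 30% | 2.04 | 5.04 | 1.05-1.08 | 1.03-1.05 |
| 40% | 1.44 | 4.44 | 1.04-1.06 | 1.02-1.04 |
| 50% | 0.99 | 3.99 | 1.03-1.04 | 1.02 |

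The 20%-40% rows correspond to the article's 60%-80% ever reassessed (50% plus 10%-30%). The 50% row counts only those reassessed within 12 months. The last column shows that stopping the series at 2021 shrinks the artefact but does not remove it.

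**Informative exit.** Same entry window; 20% impaired at entry; exit 25% a year if unimpaired and 50% or 60% if impaired; new impairment 5% or 10% a year (all assumed).

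| Exit if impaired | New impairment | Prevalence 2012 → 2021 → 2024 | OR per year |
|---|---|---|---|
| 50% | 5% | 20% → 18% → 16% | 0.98 |
| 50% | 10% | 20% → 24% → 28% | 1.03 |
| 60% | 5% | 20% → 16% → 12% | 0.96 |
| 60% | 10% | 20% → 21% → 21% | 1.00 |

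With equal exit of 30% in the same two-state set-up, the OR is 1.06-1.09.

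**Does the remedy work?** A separate simulation used exponential stays with means of 2, 3 and 4 years, 20% prevalence at entry, log-odds rising 0.25 per year since entry, and no calendar trend. An independence GEE gave these ORs per year for mean stays of 2, 3 and 4 years:
- year alone: 1.062 (95% CI 1.057-1.067), 1.086 (1.081-1.090), 1.102 (1.098-1.106)
- year plus time since first assessment: 1.001, 0.996, 0.999
- first assessments only: 1.009, 0.998, 1.003

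With about 98,000 to 153,000 assessments per fit, the false trends were estimated tightly. Under the same assumptions, a population open to entry throughout showed flat prevalence.

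**The case against.** **The quoted purpose concerns social determinants, and the section's own examples are sex and a deprivation quintile.** That stands as a limit: for those variables the drift should be small. The section nevertheless fits one model per characteristic, and the list includes ones that change with time in care.

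**A reader might infer that the plan will report a significant worsening of clients.** The documents do not support a direction. Follow-up ends at care home admission or death, and impaired people may leave faster. With such exit the apparent OR ran from 0.96 to 1.03. Mean age is more likely to rise, but for disability and cognition the artefact could be upward, absent or downward.

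**A reader might also infer that the artefact distorts the choice of propensity score covariates.** This is not shown. Those covariates are chosen by whether attendees and eligible nonattendees differ, which is the class contrast and not the year term. The point does not reach that step.

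**Initial RAI-HC might mean first within the window rather than first ever.** Prevalent clients would then fill 2012 and the early drift would largely vanish. The section on matching variables, however, treats a nonattendee's first RAI-HC as admission to long-term home care. On either reading the closure after 2021 remains: in the simulation with a 3-year mean stay and the first-in-window reading, prevalence still went from 33% in 2021 to 49% in 2024.

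**The objective asks how the number of people with each characteristic changes, not how entrants change.** That is fair: initial assessments alone answer a narrower question and miss records nearer to actual attendance. They should supplement the repeated-assessment model, not replace it.

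**A fuller analysis plan may add terms.** Possibly, but the article names the model terms and assigns a meaning to the year term, and that meaning does not hold for this cohort. The covariate adjustment it describes elsewhere belongs to Objective 3.

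**Conclusion.** The concern holds for characteristics that change with time since entry. The confounding of calendar year with time in care follows from the entry and follow-up dates together with the listed model terms, and needs no assumption. Its size does: an OR per year of about 1.04-1.10 with exit unrelated to the characteristic at 20%-40% a year, about 1.03-1.04 at 50%, and 0.96-1.03 if impaired people leave faster. All of these rest on an assumed 20% prevalence at entry, constant entry and the assumed progression rates. Neither magnitude nor sign can be fixed from the article. The point bears on a descriptive objective; no effect on the Objective 3 estimates has been shown. It should be corrected before Objective 2 trends are reported.

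**What to change.** 1. Add time since first RAI-HC, and its interaction with use class, to the Objective 2 GEE models. Entry is staggered, so year and time since entry can be estimated together. Year then compares calendar years at the same time since entry. A flexible form (for example, categories) is safer than a straight line.
2. Estimate secular change among entrants from initial RAI-HCs, one record per person, 2012-2021, and label it as such.
3. In the quarterly plots, mark 2022-2024 as closed to entry, or stratify by time since entry. Cutting the plots at 2021 is optional and does not suffice alone.

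The cost is one or two extra model terms, slightly less precise year estimates and a change of wording. The first-assessment date is already needed for the cohort and exposure definitions, so no new data are required.

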#### Propensity Score–Matching Variables

To compare outcomes between day program attendees and nonattendees, we will use propensity score matching [78] (for details, see Statistical Analyses section). Propensity scores aim to ensure a similar distribution of baseline variables among treatment (day program attendees) and control (nonattendees)—akin to what random assignment aims to accomplish in randomized trials [78]. Since we lack evidence on differences between day program attendees and nonattendees, our objective 2 analyses will be key to informing the selection of the exact covariates that will form the propensity score. We will derive covariates for day program attendees from the RAI-HC day program eligibility assessment (index date). For each day program attendee, we will identify potential matches as nonattendees whose first RAI-HC assessment was completed within ±3 months of the attendee’s index date (ie, admission to long-term home care at about the same time). This RAI-HC assessment will provide the relevant covariates to enable propensity score matching with day program attendees as of their index date.

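### Objective 2 assigns its two main questions to the class and year terms of a model containing their interaction; under ordinary reference coding these terms answer narrower questions

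*Protocol article*

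**What the plan says.** The Objective 2 section of the Protocol article first states what the GEE is for: "we will assess whether the number of persons with each characteristic has changed over time and whether characteristics are associated with older adults’ day program" attendance pattern, nonattendance included. Both questions are put without condition on a particular year or class.

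It then describes the model. "We will run a separate GEE model for each characteristic within each province, with the respective characteristic as individual-level outcome". Models account for repeated measures and "include the independent variables year of assessment (to assess change in social determinants over time"), then "use or nonuse class (to assess differences in social determinants by day program use), and an interaction between year and use or nonuse". Only the interaction is described as year-specific; its purpose is "to assess how social determinants differed between use and nonuse patterns by year". On combining results, the section says: "Using random-effects mixed regression models, we will pool provincial effects statistically". It does not say which estimate is pooled.

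The section on propensity score–matching variables makes the results matter for Objective 3: "our objective 2 analyses will be key to informing the selection of the exact covariates that will form the propensity score".

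**The concern.** The plan gives each term of one model its own question. That mapping is right for the class and year terms when the model has no interaction. Once the interaction is included, what those two terms estimate depends on how class and year are coded. Under reference coding, the usual software default, each is conditional on the other variable being at its reference value.

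An analyst who follows the description literally would report the class coefficients as the differences by use and the year coefficient as the change over time. A characteristic that separates attendees from nonattendees over most of the study could then be reported as not different, or the reverse.

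Three features of this study make it worth settling in advance:

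- The data cannot leave each province, so analysts fit the models separately with shared programs, and only what those programs output can be pooled.
- The second set of matching covariates consists of characteristics that Objective 2 shows to differ between the groups.
- If 2012 is the reference year, only people first assessed in 2012 contribute to it, so the reference difference would rest on relatively few assessments.

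**Working it through.** The plan gives no figure on this point, so there is none to reproduce. The check is algebra, followed by an illustration on assumed data.

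**Algebra.** For one use class against nonuse:

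logit P = b0 + b1·class + b2·year + b3·class·year

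- Class difference in year t: b1 + b3·t. The coefficient b1 is this difference at t = 0, the reference year.
- Trend in nonusers: b2. Trend in users: b2 + b3. The coefficient b2 is the trend in the reference class.
- Class difference averaged over the observed years, on the log-odds scale: b1 + b3·(mean year).
- Trend averaged over classes: b2 + b3·(weight given to users).

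So b1 = 0 means no difference in the reference year, and b2 = 0 means no trend in the reference class. The plan's questions correspond to the last two lines.

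**Illustration.** None of these inputs comes from the documents:

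- 6,000 people in three classes: nonuse 60%, use A 25%, use B 15%.
- Years 0 to 9, with one to three yearly assessments per person.
- A person-level effect with SD 0.7 on the log-odds scale.
- No class difference in year 0; the log-odds difference then grows by 0.10 per year in both use classes. No trend in nonusers.
- Logistic GEE with exchangeable working correlation.

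Estimates with reference coding and year starting at 0:

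| Term | Estimate | SE |
|---|---|---|
| Class A | 0.0004 | 0.0970 |
| Class B | 0.0290 | 0.1158 |
| Year | −0.0022 | 0.0110 |
| A × year | 0.1020 | 0.0201 |
| B × year | 0.0913 | 0.0239 |

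With year centred, the class A coefficient becomes 0.4263. The implied mean year is (0.4263 − 0.0004) / 0.1020 = 4.18. For class B, 0.0290 + 0.0913 × 4.18 = 0.41, which matches the fitted 0.4100.

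The three class trends are −0.0022, −0.0022 + 0.1020 = 0.0998 and −0.0022 + 0.0913 = 0.0891. Their equal-weight average is 0.1867 / 3 = 0.0622, which is the year coefficient under sum-to-zero coding. Weighted by the assumed class shares, the average is 0.60 × (−0.0022) + 0.25 × 0.0998 + 0.15 × 0.0891 = 0.037. The weights therefore need stating too.

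Tests on the same data:

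| Question | Test | Chi-square (df) | p |
|---|---|---|---|
| Class | Reference coding | 0.07 (2) | 0.97 |
| Class | Year centred | 101.4 (2) | 9e-23 |
| Class | Class and interaction jointly | 134.1 (4) | 5e-28 |
| Year | Nonuse as reference | 0.04 (1) | 0.84 |
| Year | Sum-to-zero class coding | 40.7 (1) | 2e-10 |
| Year | Year and interaction jointly | 52.7 (3) | 2e-11 |

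With year categorical, the class terms give p = 0.78 under reference coding and p = 6e-21 under sum-to-zero coding.

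**Errors in both directions.** A second simulation assumed 20,000 assessments, 25% of them from users, over 2012–2024, with year coded from 2012, 70% yearly retention and alpha .05:

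- Groups equal in 2012, then diverging by OR 1.03 per year: the class term rejects in 4% of runs, the averaged contrast in 100%.
- No difference at the average assessment year, but crossing slopes (OR 0.97 per year): the class term rejects in 67%, the averaged contrast in 6%.
- Users change by OR 1.05 per year and nonusers do not: the year term rejects in 5%, the averaged trend in 76%.

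The low rates in the first and third scenarios are built in, because the quantity tested is set to zero there. Within-person correlation was left out; it does not alter which contrast is tested.

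**Pooling.** The variance of b1 + b3·m is Var(b1) + m²·Var(b3) + 2m·Cov(b1, b3). If a province exports only coefficients and standard errors, the covariance is missing and the averaged contrast cannot be rebuilt centrally with a correct standard error.

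**The case against.** The strongest reply is that the article fixes no coding. It does not say whether year is linear or categorical, how class is coded, or whether inference comes from single coefficients, joint tests or marginal contrasts. Centred year, sum-to-zero coding or marginal contrasts would give averaged effects from the same model, as the tables show. Such details are commonly left to an analysis plan or to the shared programs, and naming the purpose of each variable is a normal condensed description. This much stands: a reader might infer that the plan necessarily tests only the reference year and reference class, and the text does not support that. The result follows from reference coding, not from the interaction alone. What the reply does not remove is that the article goes beyond silence on coding. It ties each question to a term, and that tie fails under the most common coding.

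A second reply is that little is lost downstream. A reader might infer that a difference missed here becomes an uncontrolled confounder in Objective 3. The documents do not support that either:

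- The eligibility covariates form the first matching set whatever Objective 2 finds.
- Proportions with confidence intervals are plotted by quarter, province and class, so a divergence over time would be visible.
- Covariates that differ between attendees and nonattendees at P ≤ .15 in bivariate comparisons are considered for the Objective 3 outcome models.
- No rule ties covariate selection to the p value of one coefficient, and the second matching set compares attendees with potentially eligible nonattendees, a narrower group than the full Objective 2 cohort.

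These points limit the harm to Objective 3. They do not correct the inferential statements of Objective 2 itself or the pooled estimates.

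**Conclusion.** The point holds conditionally. Under ordinary reference coding, without centring, effect coding or marginal contrasts, the terms to which the plan assigns its two main Objective 2 questions estimate the class difference in the reference year and the trend in the reference class. The reported and pooled effects would then not answer those questions, and could misinform the choice of second-set propensity score covariates.

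The size in this study cannot be derived from the documents. It depends on how far class differences change over the years and on the coding adopted. The p values and rejection rates above rest on assumed inputs and show only that one model and one dataset can lead to opposite conclusions. The consequence for Objective 3 is limited. The change is still worth making, because it stops the main Objective 2 results from depending on a software default.

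**What to change.** 1. Keep the model with the interaction, and use the interaction for differential change only.
2. Base the conclusion on differences by use on each class-versus-nonuse contrast averaged over the observed years, and the conclusion on change over time on the trend averaged over classes. State the scale and the averaging weights. Alternatively, fit the model without the interaction for these two questions.
3. Have each province output these averaged contrasts with their standard errors, and pool those.
4. Use the averaged class contrast when Objective 2 informs the choice of propensity score covariates.

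The cost is one or two sentences in the plan and a post-estimation contrast in the shared program. No new data are needed. It should be settled before the provincial programs run, since the covariances needed to rebuild the contrasts later may not be exported.
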